Effect of remote ischemic preconditioning on exercise capacity in patients with heart failure: a double blind randomized control trial

Background and Rationale:

# Remote Ischemic Preconditioning

Remote ischemic preconditioning (RIPC) is the process in which a transient, sub-lethal reduction in blood flow and oxygen delivery to tissues in one area of the body offers protection to other remote tissues from a subsequent episode of sustained ischemia. For example, animal studies have convincingly demonstrated that periodic peripheral limb ischemia, typically four cycles of 5 minutes each, followed by 5 minutes of reperfusion, reduces myocardial injury following cardiopulmonary bypass and decreases ischemia-reperfusion injury in the setting of myocardial infarction. Human studies in children and adults undergoing elective cardiac surgery have shown that three to four x 5-minute cycles of limb ischemia induced by blood pressure cuff inflation results in significantly less post-operative myocardial injury. In another recent study of adults undergoing elective percutaneous coronary intervention, RIPC was associated with less pain, less myocardial damage, and decreased major adverse cardiovascular events at 6 months. RIPC with this technique has been used in a variety of other clinical experiments with no known adverse effects, and therefore remains an attractive, non-invasive intervention with significant therapeutic potential. While the precise mechanisms are not known, available evidence suggests that factors are released into circulation during the preconditioning stimulus that exert their effects via intracellular kinases and alterations in mitochondrial function.

Expanding the concept that RIPC acts as a modulator of end-organ metabolism, the effects of ischemic preconditioning were recently tested in a model of exercise induced arterial hypoxemia in elite swimmers. Because swimmers must hold their breath during different phases their stroke cycle, their ventilation becomes limited in relation to metabolic demand, resulting in appreciable decreases in the arterial partial pressure of oxygen. It was therefore hypothesized that the effects of exercise induced arterial hypoxemia may be ameliorated, in part, by ischemic preconditioning. Notably, in a randomized controlled trial, four cycles of blood pressure cuff-induced ischemia for 5 minutes each resulted in significantly improved competitive swim times compared to sham controls in these athletes. This suggests that RIPC may provide a stimulus that helps buffer cardiac, respiratory and peripheral skeletal muscles under hypoxic conditions. Conceptually then, ischemic preconditioning may have salutary effects in other populations, including patients with heart failure for whom exercise limitations have important prognostic implications.

# Exercise Capacity in Heart Failure

The study described in detail below will examine the possible effects of RIPC in patients with left ventricular systolic dysfunction and symptomatic heart failure. Despite advances in pharmacologic and device-based therapies, patients with heart failure continue to be burdened with exertional fatigue, dyspnea and exercise intolerance. These symptoms, along with objective findings of diminished exercise capacity are unequivocally associated with decreased quality of life and worsened survival. Peak oxygen consumption (peak VO2) and measures of ventilatory efficiency during exercise remain powerful predictors of mortality or need for cardiac transplantation and/or mechanical circulatory support.

Exercise intolerance in heart failure patients is thought to be multi-factorial. Assuming normal pulmonary gas exchange, VO2 is a function of cardiac output and skeletal muscle oxygen uptake and metabolism, both of which are impaired in the setting of heart failure. During exercise, the inability to adequately increase cardiac output and skeletal muscle blood flow is associated with early anaerobic metabolism, lactic acid production and muscle fatigue, commensurate with restricted peak VO2. Compounding this circulatory dysfunction, patients with heart failure typically develop adverse changes in skeletal muscle physiology. For example, there is generalized muscle atrophy over time, a decreased proportion of fatigue-resistant type I muscle fibers, and alterations of mitochondrial function leading to inefficient use of high-energy phosphates. As such, the alterations in peripheral muscle structure and function result in impaired VO2, even if cardiac output is increased pharmacologically with the administration of inotropes or vasodilators.

Aerobic fitness training as a means of conditioning the cardiovascular system and improving skeletal muscle function has been shown to improve quality of life, exercise duration, VO2, and other indices of exercise performance. More recently, in the HF Action study, a 2300 patient randomized controlled trial of exercise training versus usual care in patients with heart failure and reduced ejection fraction, exercise training was associated with a 10% reduction in mortality or cardiovascular hospitalization after adjusting for other prognostic variables. If ischemic preconditioning as a therapeutic intervention was found to improve exercise capacity in the heart failure population, it could translate into significant clinical benefits. RIPC has not previously been studied in patients with heart failure, and therefore merits evaluation.

**Research Purpose**

The main purpose of this pilot study is to determine whether RIPC affects measures of exercise capacity in patients with non-ischemic left ventricular dysfunction and symptomatic heart failure. Differential effects on various exercise performance measures could also provide mechanistic insights into the benefits seen with RIPC.

A secondary aim of the study is to determine whether the protective humoral factor, known to be released into the bloodstream of healthy individuals during RIPC, is similarly released by patients with heart failure. This will require a sub-study of the effect of dialysed patient plasma on explanted mice hearts in a Langendorff preparation. Any protective effects of RIPC in our Langendorff heart model will be correlated with exercise performance in heart failure patients.

If we find that RIPC is associated with improvements in cardiac and skeletal muscle function and exercise capacity in this study, we plan on conducting a larger randomized controlled trial to assess the therapeutic effects RIPC on clinical outcomes in a broader spectrum of heart failure patients.

Study participants would include patients followed in the Heart Function Clinic at the Toronto General Hospital, a referral center for heart failure management and cardiac transplantation evaluation. This multidisciplinary clinic actively follows approximately 850 patients and sees 25-30 new referrals per month. Clinic patients undergo routine assessment, including cardiopulmonary exercise testing by a trained exercise physiologist at regular intervals as dictated by clinical circumstances. In general, the target population has a baseline risk of death in excess of 30% per year and would be expected to have at least a moderate impairment in exercise capacity. Consequently, Heart Function Clinic patients represent an ideal sample population in which to study the effects of RIPC on exercise performance.

## Hypothesis

1. We hypothesize that RIPC induced by transient upper limb ischemia will improve exercise performance measures in patients with non-ischemic cardiomyopathy and symptomatic heart failure.
2. Langendorf mouse heart preparations perfused with dialysed plasma from patients after RIPC treatment will be more resistant to ischemic injury than mouse heart preparations perfused with dialysed plasma obtained after ‘sham’ RIPC.

**Methods**

*Study Design*

This pilot study will be a randomized double blind cross-over trial of RIPC in ambulatory heart failure patients undergoing cardiopulmonary stress testing. One-half of study patients will be randomly assigned to RIPC treatment in the first session, and the second half of the patients will receive sham preconditioning prior to exercise testing. The following week, patients will undergo whichever protocol they had not completed in the first session, prior to repeat exercise testing. In this manner, patients will be exposed to both the RIPC and sham treatments.

Investigators and patients will be blinded to treatment allocation. The specific RIPC intervention will include four 5-minute cycles of upper limb blood pressure cuff inflation to 20mmHg above systolic blood pressure to induce forearm ischemia. Each 5-minute cycle of ischemia will be followed by 5 minutes of reperfusion (blood pressure cuff fully deflated). The sham-control arm similarly will include four 5-minute cycles of blood pressure cuff inflation to 10mmHg only, interspersed with 5 minutes of cuff deflation. Following blood sampling (see below), the, patients will then perform a routine cardiopulmonary exercise test under the supervision of a single dedicated exercise physiologist who will be blinded to treatment assignment.

The cardiopulmonary exercise study consists of a standard stationary bicycle ramp protocol in which workload increases by 10 watts per minute. The study is symptom- limited once a target respiratory exchange ratio (RER) of  1.05 is achieved. The RER  1.05 indicates that the patient has exercised with sufficient intensity to induce lactic acidosis as a byproduct of anaerobic metabolism. The exercise study would also terminated prematurely for any of the following: hypotensive response ( 10mmHg drop in systolic blood pressure) to increasing work load, lightheadedness, signs of poor perfusion, signs of significant ischemia on the ECG ( 2mm horizontal/downsloping ST segment depression or  1mm ST segment elevation in non-infarct leads), significant brady or tachyarrhythmia including ventricular tachycardia, hypertensive response to exercise (systolic blood pressure ≥250 mmHg or diastolic blood pressure  110mmHg) or upon patient request.

# Study Patients

Ambulatory patients from the Toronto General Hospital Heart Function Clinic scheduled for routine cardiopulmonary stress test will be approached and offered participation. Appropriate patients will meet the following inclusion and exclusion criteria:

Inclusion criteria:

Male and females >18yrs of age

Non-ischemic cardiomyopathy

LV ejection fraction <40%

New York Heart Association functional class II-IV

Clinically stable

Exclusion criteria:

Recent cardiovascular hospitalization within the previous 4 weeks

New heart failure diagnosis within previous 12 weeks

Ischemic cause for cardiomyopathy or active ischemia

Diabetes mellitus

Peripheral neuropathy

Not able to ambulate or complete exercise bicycle protocol for non-cardiovascular reasons

Presence of a ventricular assist device

Uncontrolled brady or tachyarrythmias

Uncontrolled hypertension (systolic blood pressure ≥ 200mmHg)

Severe obstructive valve lesion

Significant LV outflow tract gradient

Aortic dissection

Acute myocarditis/pericarditis

Baseline clinical characteristics will be collected, including age, gender, heart failure duration and etiology, last available LVEF, NYHA functional class, history of hypertension, atrial fibrillation/flutter, pacemaker/biventricular pacemaker, implantable defibrillator, non-cardiac comorbidities, medications, weight, height, blood pressure, heart rate, serum creatinine, sodium, BNP.

# Study Endpoints

Clinical endpoints will be ascertained at the conclusion of the cardiopulmonary stress test. The primary endpoint will be peak VO2 in patients achieving a respiratory exchange ratio >1.05. Secondary endpoints include other measures of exercise performance: ventilatory threshold, peak VE/VCO2 slope, workload achieved in Watts, total exercise time and oxygen uptake efficiency slope. We will also assess serum lactate post stress to directly determine the effect of RIPC on lactic acid production under anaerobic conditions.

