# Sub-study Design

*i) Preparation of plasma dialysate:*

25 of blood will be taken after the RIPC or sham RIPC protocol has been completed. Each sample will be anonymised and coded according to treatment assignment, stored on ice and transferred to the [name] laboratory in the MacMaster building, Sickkids. Subsequently, the plasma fraction will be separated by centrifugation (3,000 *g* for 20 min). To prepare dialysate, 12-15 of plasma will be placed in dialysis tubing with a 12-14 kDa cut-off membrane (Spectrapor, USA), dialysed against a 20 fold volume of Krebs buffer (240-300 mL) while stirred overnight at 4oC, and stored at -80oC**.** Prior to perfusion of the mouse hearts, D-glucose, NaHCO3 and EDTA are added to a final concentration of 15mM, 25 mM and 0.5mM, respectively to the dialysate.

*ii) Mouse langendorff:*

After a 20-min stabilization period, isolated hearts will be perfused for 30 min using dialysate, then washed out for 5min, and then subjected to 30 min of no-flow global ischemia followed by 60min of reperfusion. HHeHemodynamic measurements, including heart rate (HR), peak left ventricular pressure (LVP), maximum rate of contraction (+dP/dtmax), maximum rate of relaxation (-dP/dtmin), and LVEDP will be recorded on a data acquisition system (PowerLab, ADInstruments) throughout the procedure. Coronary flow rate will be calculated by measuring the amount of effluent emerging from the heart per minute (ml/min). Myocardial infarction size will be measured in heart slices stained with 1.25% triphenyltetrazolium chloride (TTC) in 200mM Tris pH 7.4 for 15 min in 37oC water bath. Afterfixation for 4-6 hours in 10% neutral buffered formaldehyde, both sides of each slice will photographed by electronic scanning (CanoScan 4400F) and the infarct area measured by automated planimetry using Adobe Photoshop® CS2 software. All personnel involved in the preparation and assessment will be blinded to treatment assignment.

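### Post-stress lactate does not directly determine the effect of RIPC on lactic acid production, because the two tests can end at different, treatment-dependent workloads

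*Protocol*

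**What the plan says.** After listing the primary and secondary endpoints, the Study Endpoints section of the protocol adds serum lactate: "We will also assess serum lactate post stress to directly determine the effect of RIPC on lactic acid production under anaerobic conditions". On timing, the same section says only that "Clinical endpoints will be ascertained at the conclusion of the cardiopulmonary stress test". It gives neither the number of post-stress draws nor an interval after exercise.

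The Methods section describes the test as a "standard stationary bicycle ramp protocol in which workload increases by 10 watts per minute". On when it ends: "The study is symptom- limited once a target respiratory exchange ratio" of 1.05 is achieved. Reaching that target, the protocol says, "indicates that the patient has exercised with sufficient intensity to induce lactic acidosis as a byproduct of anaerobic metabolism".

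The first hypothesis is that RIPC "will improve exercise performance measures in patients with non-ischemic cardiomyopathy and symptomatic heart failure". The secondary endpoints accordingly include "workload achieved in Watts, total exercise time and oxygen uptake efficiency slope".

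The only other blood draw described is the one for the dialysate sub-study: "blood will be taken after the RIPC or sham RIPC protocol has been completed". Methods places it before exercise. No lactate measurement is assigned to it, and no lactate at a fixed workload or fixed time is described anywhere.

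**The concern.** The respiratory exchange ratio target is a floor on effort and not a common stopping point. Beyond it, each test runs on while the ramp climbs 10 W every minute, and the protocol itself says that anaerobic metabolism is by then producing lactic acid. A patient who lasts longer after RIPC does more work in that range.

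Post-stress lactate then carries two effects. One is any change in the lactate produced at a given workload, which is what the endpoint claims to show. The other is any change in the workload reached, which the trial lists as an outcome in its own right. Blinding and the cross-over do not separate them, because final workload is itself affected by treatment.

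What is at stake is a wrong mechanistic statement. Equal or higher lactate after RIPC could be reported as showing no metabolic benefit, or harm, when lactate at every workload was in fact lower. An analysis plan could not fully repair this if only post-stress samples exist, because adjusting for final workload conditions on a post-treatment variable.

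**Working it through.** **The plan's own figures.** The protocol gives no figure for lactate. Its sample size concerns peak VO2 only. It reproduces as 2 × (1.96 + 0.842)² × 2.5² / 1.5² = 43.6, so 44 measurements per condition if a patient's two sessions are taken as uncorrelated. It has no bearing on the lactate claim. The target effect also reproduces: 1.5/15 = 10.0% and 1.5/14 = 10.7%, matching the stated change of about 10%.

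**Inputs from the protocol:** ramp 10 W/min; target gain in peak VO2 about 10%.

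**Inputs assumed (not in the protocol):**
- sham peak workload P = 80 to 100 W
- resting-level lactate 1.5 mmol/L up to a threshold at 55% of P
- above the threshold, a linear rise of s = 0.05 to 0.12 mmol/L per W
- a gain in peak workload after RIPC of g = 10%, with 5% and 15% as variants

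The 10% borrows the peak VO2 target. As a rough check, 1.5 mL/kg/min at an assumed 70–90 kg and 9–11 mL O2/min per W is 1.5 × 70 / 11 = 9.5 W to 1.5 × 90 / 9 = 15.0 W. That is of the same order as 10% of 80–100 W (8–10 W). It takes the whole gain as extra watts.

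**Model.** Let c be the proportional fall in slope under RIPC.
- Sham: 1.5 + s × 0.45P
- RIPC: 1.5 + (1 − c) × s × (0.45 + g)P
- Difference: sP × [(1 − c)(0.45 + g) − 0.45]

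With g = 10% the ramp lasts 8/10 = 0.8 to 10/10 = 1.0 min longer. The low end below uses sP = 0.05 × 80 = 4, the high end sP = 0.12 × 100 = 12.

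| Slope reduction c | Bracket | RIPC − sham lactate (mmol/L) |
|---|---|---|
| 0% | 0.55 − 0.45 = 0.100 | +0.4 to +1.2 |
| 10% | 0.495 − 0.45 = 0.045 | +0.18 to +0.54 |
| 18.2% | 0.45 − 0.45 = 0 | 0 |
| 30% | 0.385 − 0.45 = −0.065 | −0.26 to −0.78 |

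**Break-even.** The difference is zero at c = g/(0.45 + g):
- g = 5%: 0.05/0.50 = 10%
- g = 10%: 0.10/0.55 = 18.2%
- g = 15%: 0.15/0.60 = 25%

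In this model the break-even does not depend on s or P, only on the workload gain and the assumed threshold.

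**Reading.** In the last three rows of the table RIPC lowers lactate at every workload above the threshold, yet the observed difference is positive, zero or negative. The sign of the raw difference does not identify the effect on production.

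**The case against.** The strongest case on the other side has four parts.

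- Lactate is an add-on to a pilot. No power statement, decision rule or primary conclusion depends on it. This stands, and it limits the weight of the point.
- Lactate after maximal effort in the same patient, with and without RIPC, is a legitimate descriptive comparison. The protocol speaks of anaerobic conditions, which it ties to the ratio target, and not of equal work. This stands for description. It does not rescue the claim that the comparison directly determines an effect on production.
- Workload and exercise time are recorded in the same test, so a reader can see whether the sessions ended at the same point. This also stands, and the fix uses it. The protocol does not, however, say that lactate will be read together with them.
- Every lactate magnitude above is assumed. This is true. The figures illustrate the argument, which itself needs only the symptom-limited ramp and a treatment expected to change how far patients exercise.

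A reader might also go further than the protocol allows:

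- *A true benefit must raise end-exercise lactate.* It need not; the table shows a fall once the slope reduction is large enough.
- *Only one sample is drawn.* The protocol gives neither number nor timing.
- *Cuff ischemia alters resting lactate before exercise.* This is possible but not documented, and each ischemic cycle is followed by 5 minutes of reperfusion.
- *The mechanistic aim in Research Purpose fails.* That section does not mention lactate. It rests on differential effects across the exercise measures, which include ventilatory threshold.

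**Conclusion.** The statement is wrong as written. Post-stress lactate, taken after tests that can end at different and treatment-dependent workloads, does not directly determine the effect of RIPC on lactic acid production. The RIPC–sham difference can rise, stay equal or fall even if RIPC truly lowers lactate at each workload. With a 10% workload gain, the illustrative model turns from positive to negative at a slope reduction of about 18%; for gains of 5% and 15% the turning point is 10% and 25%. These sizes rest wholly on the assumed threshold and linear rise, while the structural conclusion does not.

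It would be too strong to call the endpoint uninformative. Lower lactate at an equal or higher workload would still suggest reduced production; it is equal or higher lactate at a higher workload that is ambiguous. The primary endpoint and its analysis are not touched.

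**What to change.** In Study Endpoints:

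1. Remove the words *directly determine*. Describe raw post-stress lactate as an exploratory, descriptive measure, always reported with the workload achieved and total exercise time of the same session.
2. State that only lower lactate at an equal or higher workload will be read as suggesting reduced lactate production, and that equal or higher lactate at a higher workload will not be interpreted as an effect on production.

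The second rule still depends on a post-treatment workload, so it supports a suggestion and not a test. For the same reason, dividing lactate by watts or adjusting for peak workload is not a clean substitute. Lactate at a matched submaximal workload would address the question more closely, but it needs an extra draw during exercise and is not required for this correction.

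Optionally, measure lactate at the existing pre-exercise draw to account for any resting difference. A small extra tube is safer than assuming spare blood, since the sub-study uses that draw for dialysate. This does not remove the unequal-workload problem.

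**Cost:** a few sentences, and for the option one tube and one assay per session. The downside is a weaker mechanistic statement from this add-on endpoint.

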# Sample Size and Data Analysis

This pilot study will be conducted with a sample size of 44 patients to determine baseline exercise parameter and variance values in our study population. Assuming that our patients are similar to contemporary heart failure patients evaluated in exercise training trials, mean baseline exercise peak VO2 is expected to be approximately 14.0 –15.0 mL/kg/min, with an estimated standard deviation of 2.5 mL/kg/min. A 44 patient cross-over trial would therefore provide 80% power to detect a difference of 1.5 mL/kg/min, which represents a clinically significant ~10% change in peak VO2 (2-tailed alpha level 0.05).

Continuous variables will be summarized using means and standard deviations and contiguous variables will be summarized as proportions. Student’s T test and chi squares will be used to determine differences between continuous and categorical variables, respectively. Pre-specified subgroup analyses will assess the effect of RIPC on patients with moderately severe exercise limitation (sham peak VO2 <14mL/kg/min) or very severe exercise limitation (sham peak VO2 <10mL/kg/min), as well as its effect on patients taking beta blockers versus those not taking beta blockers.

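### The cross-over is to be analysed by Student's t test with no statement that it is paired and no allowance for period; read as a two-sample test, its confidence interval would be 1.4 to 3.1 times too wide

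*Protocol*

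**What the plan says.** The Study Design text under Methods is clear about the structure: "This pilot study will be a randomized double blind cross-over trial of RIPC". Allocation is to sequence: "One-half of study patients will be randomly assigned to RIPC treatment in the first session", and the other half start with sham. Then "The following week, patients will undergo whichever protocol they had not completed in the first session, prior to repeat exercise testing". Every patient therefore gives one exercise test under each condition, a week apart.

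Study Endpoints defines the primary outcome: "The primary endpoint will be peak VO2 in patients achieving a respiratory exchange ratio >1.05". The secondary endpoints (ventilatory threshold, VE/VCO2 slope, workload, exercise time, oxygen uptake efficiency slope) and post-stress lactate are also continuous.

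Sample Size and Data Analysis states that "This pilot study will be conducted with a sample size of 44 patients", and that one purpose is to establish variance values in this population. It assumes an SD of 2.5 mL/kg/min, given for baseline peak VO2, and claims 80% power for a difference of 1.5 at two-sided alpha 0.05. For inference it says that Student's "T test and chi squares will be used to determine differences between continuous and categorical variables, respectively". Pairing, within-patient differences, period and sequence are not mentioned anywhere in the protocol.

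**The concern.** A cross-over gains its precision by removing between-patient variation from the treatment comparison. A two-sample t test on the RIPC and sham values puts that variation back into the error term. The estimate itself is unchanged with complete pairs, but the interval is too wide, the p-value too large, and a real effect somewhat smaller than planned may be reported as null.

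Two further things are at stake. First, a two-sample analysis never estimates the within-patient variance. The protocol names variance values as an aim, and any further cross-over on exercise capacity would need that one. Second, even a paired t test leaves out period, although each patient repeats the same exercise test a week later.

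This is not a detail left to a statistical analysis plan. The protocol names the test, and the name does not settle which of two quite different analyses is meant.

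**Working it through.** **Inputs from the protocol** (Sample Size and Data Analysis): n = 44 patients, SD σ = 2.5, difference 1.5, two-sided alpha 0.05, power 80%. The within-patient correlation ρ is not given, so I assume 0.5 to 0.9. I also assume the same SD under both treatments.

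**Step 1. Reproduce the 44.**
2(1.960 + 0.842)² × 2.5² / 1.5² = 43.6, rounded up to 44. Two routes lead to this figure:
- the per-group size for two independent groups (power 80.4% with 44 per group);
- the total for a 2×2 cross-over if 2.5 is taken as the within-patient SD, which is the same as a paired calculation with ρ = 0 (SD of differences 2.5√2 = 3.54).

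Reading 2.5 as the SD of differences gives 22, not 44. Neither route that gives 44 credits pairing, because the text offers 2.5 as the SD of baseline peak VO2.

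**Step 2. Standard errors and 95% CI half-widths with 44 complete pairs.**
Two-sample: SE = 2.5√(2/44) = 0.533. With t on 86 df (1.988), the half-width is 1.06 for every ρ.
Paired: SE = 2.5√(2(1−ρ))/√44, with t on 43 df (2.017).

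| ρ | Paired SE | Paired half-width | Two-sample half-width | Ratio of half-widths |
|---|---|---|---|---|
| 0.5 | 0.377 | 0.76 | 1.06 | 1.4 |
| 0.7 | 0.292 | 0.59 | 1.06 | 1.8 |
| 0.8 | 0.238 | 0.48 | 1.06 | 2.2 |
| 0.9 | 0.169 | 0.34 | 1.06 | 3.1 |

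**Step 3. Type I error of the two-sample test.**
The mean difference really varies with the paired SE, but is judged against ±1.06. The actual two-sided error, 2[1 − Φ(1.06/SE paired)], is 0.5% at ρ = 0.5, 0.03% at 0.7 and about 0.001% at 0.8, against a nominal 5%.

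**Step 4. Power.**
Two-sample: 1 − Φ((1.06 − δ)/SE paired), holding the pooled SD at 2.5. Paired: noncentral t on 43 df.

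| True difference δ | Analysis | ρ = 0.5 | ρ = 0.7 | ρ = 0.8 |
|---|---|---|---|---|
| 1.5 | two-sample | 88% | 93% | 97% |
| 1.5 | paired | 97% | >99% | >99% |
| 1.25 | two-sample | 69% | 74% | 79% |
| 1.0 | two-sample | 44% | 42% | 40% |
| 1.0 | paired | 74% | 92% | 98% |
| 0.75 | two-sample | 21% | 14% | 10% |
| 0.75 | paired | 49% | 71% | 87% |

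**Step 5. A paired t test without period.**
Let π be the shift from session 1 to session 2. The RIPC-minus-sham difference has expectation δ − π when RIPC comes first and δ + π when sham comes first.
- Equal sequences: the mean is unbiased, but the variance of the differences rises from σ_d² to σ_d² + π². At ρ = 0.8, σ_d = 1.58. The SE is multiplied by √((2.5 + 0.25)/2.5) = 1.05 for π = 0.5, and by √((2.5 + 1.0)/2.5) = 1.18 for π = 1.0. Both values of π are assumptions.
- Unequal sequences: the bias is π × (n sham-first − n RIPC-first)/(total n). The RER restriction in Study Endpoints can remove patients after randomization, so equal numbers in the analysed set are not guaranteed.

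**The case against.** The strongest reply is that the protocol never says unpaired. Student's t test includes the paired form, the design is called a cross-over in both relevant sections, and a competent analyst might well pair. That stands: a two-sample analysis is a likely reading, not a proven one.

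A reader might take the 44 as proof that a two-sample test is planned. It is not. The same figure follows from the usual cross-over formula with 2.5 as the within-patient SD. That would be a questionable input, but it says nothing certain about the test.

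A reader might also infer that any effect below 1.5 would be missed, or that the trial is underpowered. Neither follows. Even the two-sample test keeps 69% to 79% power at 1.25 and exceeds the stated 80% at 1.5 for correlations of 0.5 to 0.8. For any positive correlation the error is conservative, with no excess of false positives.

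Nor do the documents support a charge that chi-square will be misused on paired outcomes. No paired yes/no endpoint is listed, and chi-square could properly compare categorical baseline variables between groups of different patients.

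On period, it is fair to say that 1:1 sequences keep a paired t test unbiased, and that the size of any period shift is assumed. What remains is that the named test leaves the primary analysis open between two very different standard errors, and that period is not accounted for.

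**Conclusion.** The point holds as a fault of specification with a material but conservative consequence. The protocol fixes a test by name without saying that it is paired, and makes no provision for period. If the test is run in two-sample form, the 95% CI is ±1.06 mL/kg/min instead of ±0.76 to ±0.34, and power at a true difference of 1.0 falls from 74–98% to 40–44%. Power at the planned 1.5 is not endangered for correlations of 0.5 or higher. If the test is run paired but without period, the loss is smaller: an SE about 5% to 18% larger at ρ = 0.8 for an assumed shift of 0.5 to 1.0. There is bias only if a period shift and unequal sequences occur together.

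These sizes rest on the protocol's SD of 2.5, on 44 complete pairs, and on assumed correlations and period shifts that the protocol does not give. The conclusion that the wording needs correcting does not depend on their exact values.

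**What to change.** In Sample Size and Data Analysis, replace the t test for peak VO2 and the continuous secondary endpoints with a named within-patient analysis: a linear mixed model with fixed treatment, period and sequence and a random patient effect. With complete pairs, the two-sequence comparison of within-patient differences is an equivalent and simpler choice. The two differ once the RER criterion leaves a patient with only one usable session, so the text should say which is primary. Report the RIPC-minus-sham mean difference with its 95% CI, and the within-patient SD, which serves the pilot's aim of learning the variance.

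The cost is wording and one degree of freedom for period (42 instead of 43 with 44 complete pairs). No added patients, visits or measurements are needed. The change should be made before outcome data are seen by treatment.
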